**Figure 2 figure2:**
[figure not shown]
mPareshan app: the content of counseling sessions delivered by lady health workers to those who screened positive for anxiety and depression.

**Figure 3 figure3:**
[figure not shown]
Overview of mPareshan app segments. LHS: lady health supervisor; LHW: lady health worker; SC: study coordinator.

**Figure 4 figure4:**
[figure not shown]
mPareshan intervention workflow steps for implementation roll out. LHS: lady health supervisor; LHW: lady health worker; SC: study coordinator.

### Phase 3: Postintervention

#### End Line Quantitative Assessment

After the conclusion of the sixth mental health counseling session, an end line HH survey is conducted by trained data collectors using the same PHQ-9 and GAD-7 psychometric tools. This determines the change in mean symptomatic scores of anxiety and depression among intervention recipients (SPs), indicating intervention effectiveness (clinical outcome).

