## Methods

### Study Procedure Outline

Project mPareshan is a prospective, single-district, pre- and posttest implementation research trial, using mixed methods (qualitative and quantitative) of data collection. All phases of the trial are described in detail in the following sections. In the preintervention phase, formative qualitative assessments are conducted with relevant stakeholders (CPs, LHWs, LHSs, and policy makers) to determine the acceptability and appropriateness of delivering mental health counseling via a mobile app. Following this, in a baseline prevalence survey, residents of Badin District are screened by trained data collectors for symptoms of anxiety and depression using standardized psychometric scales of GAD-7 and PHQ-9, respectively. Individuals having symptoms of mild and moderate anxiety or depression are then identified as SPs. Before commencing the intervention, LHWs and LHSs are trained so that their mental health literacy, communication, and counseling skills improve. The training content is contextually adapted from the World Health Organization (WHO) mhGAP guide 2.0 (designed for nonspecialist settings) [30]. A pre- and posttraining assessment of health workers assesses improvement in their knowledge and skills. Next, the mPareshan app is developed based on stakeholder feedback acquired during the formative qualitative inquiry. The app segments and intervention contents are described below. In the intervention phase, SPs receive 1 home-based counseling session per month by LHWs over a period of 6 months. After the intervention phase, a quantitative end line assessment of the SPs is done to assess change in anxiety and depression scores. Postintervention qualitative assessments of key stakeholders determine barriers and facilitators in intervention uptake and rollout. A schematic diagram of the study procedures and expected outcomes is presented in Table 1. This study has been prospectively registered by the Australian New Zealand Clinical Trial Registry (ACTRN12622000989741). Written informed consent is taken from all participants at each stage of the study.

**Table 1 table1:** Summary of mPareshan implementation research methods: phase-wise data collection procedures and expected outcomes in Badin District, Sindh, Pakistan (2022-2023).

Research questions	Phase 1: preintervention				Phase 2: intervention		Phase 3: postintervention			Expected outcome

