#### Main Intervention: mPareshan Digital App

The mPareshan app has been designed based on feedback received from stakeholders in the formative phase. The app has 3 segments—tracking, counseling, and referral. The tracking segment records information on participant recruitment or retention and consent, and has interfaces for LHS, LHW, and study coordinator to access and record their feedback. Based on a 2-week recall, the referral segment identifies danger signs related to suicidal ideation, self-harm, and harm to others and then suggests appropriate referrals to the nearest mental health facility accordingly. In the absence of danger signs, the LHW is guided to the counseling segment of the app to deliver counseling to the SPs. This segment of the app has features of psychoeducation delivered through audio and video clips, breathing exercises, and imparts skills to cope with stress. The counseling segment has different content for each of the 6 sessions, which last around 20 minutes. An outline of the content covered in the 6 sessions is provided in Figure 2.

Prior to the commencement of the 20-minute counseling session, the LHW requests the SP to be seated in a comfortable, preferably less crowded place in the home. At the end of each session, the participant is instructed to practice breathing exercises as homework until the next session. The LHW ensures that the participant feels comfortable and consents to receiving the counseling. If the SP feels uncomfortable at any point in time, the session is discontinued.

Completion of counseling segment redirects the LHW to the section on feedback where she checks all activities that are performed in the session and records her written comments. Once submitted to the server by the LHW, the session gets locked and is passed on to her LHS for review. The LHS logs in from her portal to review all the feedback provided by the LHW and submits it to the study coordinator for a final check. The subsequent session gets unlocked for the LHW after 15 days of completion of the previous session.

These sessions coincide with LHWs’ scheduled monthly HH visits in their catchment area. The health workers assigned to the HH of SPs are trained to use configured Samsung Galaxy Tab A7 (4G; Samsung Electronics) on which the mPareshan app is downloaded. The training facilitators demonstrate how health workers are to operate tracking, referral, counseling, and feedback segments of the mobile app.

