### Sample Size Calculations

For the baseline screening survey, the sample size is calculated using OpenEpi (version 3.01; Emory University) [38]. Assuming a 30% prevalence of depression and anxiety symptoms among adults, at a 5% level of significance and 80% power, 323 people are required to assess point prevalence of depression and anxiety [39]. Catering to 10% refusals, the final sample size is 366 individuals.

For the change in mental health literacy of CHWs, a total of 72 LHSs and LHWs are required to detect a mean difference of 1.5 (SD 3.9) in pre- and posttraining knowledge and skills scores, assuming 5% significance level and 80% study power [40].

For receiving mPareshan app-based intervention, the sample size for recruitment of SPs is calculated using Medcalculator (version 19.8; MedCalc Software). Assuming a mean difference between pre- and postintervention of PHQ-9 scores of 1.5 (SD 5.6; mean score at baseline=11.61 and postintervention=10.1), the minimum sample size required at a 5% level of significance and 80% power is 112. Considering a 10% attrition rate, with some oversampling, the expected sample size is 123 for recruiting participants for the mPareshan intervention and demonstrating a reduction in symptoms [41].

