### Ethical Considerations

This study protocol has been approved by the Ethical Review Committee of Aga Khan University (ERC# 2021-6570-20015). mPareshan is an implementation research feasibility trial and is not a clinical or drug trial. No adverse events are, therefore, anticipated. Any participants exhibiting (the a priori–defined) danger signs will be immediately referred during participant recruitment or counseling phases. Written, informed consent is obtained from each participant in their local language at each phase of the study. Data are anonymized and participant confidentiality is maintained. No compensation is offered to SPs for participation in the counseling sessions.

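### The end line is tied to finishing the sixth session rather than to a set time for every enrolled participant, so the paired change may describe completers only and may overstate the change among all screen positives

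*Protocol article*

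**What the plan says.** The section End Line Quantitative Assessment fixes the timing by session: "After the conclusion of the sixth mental health counseling session, an end line HH survey is conducted by trained data collectors". It names no interval from enrolment or baseline and no window. It describes the result as the change in mean scores among those who received the intervention and treats it as the measure of effectiveness.

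The Study Procedure Outline uses a phase-level wording: "After the intervention phase, a quantitative end line assessment of the SPs is done to assess change in anxiety and depression scores". The same section gives the schedule: "SPs receive 1 home-based counseling session per month by LHWs over a period of 6 months".

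The section on the app makes the sessions sequential: "The subsequent session gets unlocked for the LHW after 15 days of completion of the previous session". It routes the health worker to counseling only when no danger signs are found, and it adds: "If the SP feels uncomfortable at any point in time, the session is discontinued". Under Ethical Considerations, participants showing "danger signs will be immediately referred during participant recruitment or counseling phases". None of these places says whether an SP who stops or is referred still receives the end line survey.

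Data Analysis specifies paired t tests or McNemar tests. Sample Size Calculations deals with loss by raising the number recruited: "Considering a 10% attrition rate", the target goes from 112 to 123. Results reports 98 SPs recruited. It does not say how many completed six sessions or how many have an end line score.

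**The concern.** A follow-up visit that depends on completing treatment can select on outcome. Here the link is visible in the design. An SP who develops danger signs is sent for referral and does not go on to counseling at that visit, and later sessions stay locked until the earlier one is completed. SPs who deteriorate are therefore less likely to reach session six. If only those who reach it are surveyed, a paired test, which uses only people with both scores, silently drops the others.

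The trial has a single arm, and the baseline score is the only comparator. No control group would share the same selection or the same elapsed time. Selection at end line and differences in the baseline-to-end-line interval therefore pass directly into the estimate, which the article presents as the change among SPs.

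**Working it through.** **1. The plan's own figure.** Inputs from Sample Size Calculations: mean PHQ-9 change 1.5, SD 5.6, 5% significance, 80% power. Two-sided testing is assumed, since the article does not state it.

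- Normal approximation: (5.6 × (1.960 + 0.842) / 1.5)² = 109.4, so 110.
- Exact paired t test (noncentral t): n = 112, power 0.802. This reproduces the stated 112.
- Attrition: 112 × 1.10 = 123.2, matching the stated 123. Dividing instead, 112 / 0.90 gives 125, a trivial difference.

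The sample size arithmetic is therefore sound and is not affected by this point.

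**2. The two timing statements side by side.**

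| Section | Trigger | Population | Time from enrolment |
|---|---|---|---|
| End Line Quantitative Assessment | sixth session concluded | intervention recipients (SPs) | none given |
| Study Procedure Outline | intervention phase over | the SPs | none given |

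The first can be read person by person (six sessions completed) or as the close of the programme. The second more naturally covers everyone. Only the person-by-person reading produces a completer analysis.

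**3. Size if end line reaches completers only.** Let f be the share of enrolled SPs without an end line score, c their mean improvement, and 1.5 the completers' improvement (the planned value).

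Mean over all enrolled = (1 − f) × 1.5 + f × c

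Overstatement = 1.5 − that mean = f × (1.5 − c)

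The article gives no value for c, so c is varied. The 10% is the plan's attrition rate; the 20% is an assumption.

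| c (improvement in those without end line) | f = 10%: all-enrolled mean | f = 10%: overstatement | f = 20%: all-enrolled mean | f = 20%: overstatement |
|---|---|---|---|---|
| 1.5 (same as completers) | 1.50 | 0 | 1.50 | 0 |
| 0 (no change) | 1.35 | 0.15 | 1.20 | 0.30 |
| −1.5 (worsening) | 1.20 | 0.30 | 0.90 | 0.60 |

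At 10% the range is 0 to 0.30 points, or 0 to 20% of the planned 1.5 (0.30 / 1.5 = 0.20). If c exceeds 1.5 the sign reverses: with c = 3 and f = 10%, 0.10 × (1.5 − 3) = −0.15, and the completer mean understates the change.

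**4. Follow-up time.** Six sessions have five gaps. The app's minimum spacing gives 5 × 15 = 75 days from session 1 to session 6; monthly visits give about 5 × 30 = 150 days. These are session spans, not follow-up times: the baseline survey precedes health-worker training and app development, so the baseline-to-end-line interval is longer and is not stated. An end line tied to a session moves with whatever pace each SP's sessions took.

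**The case against.** The strongest reply is that completer-only follow-up is an inference. No sentence excludes SPs with fewer than six sessions from the end line. The Study Procedure Outline allows an end line for all SPs, the survey is carried out by separate data collectors in households, and Results speaks of analysing the 98 SPs recruited. Discontinuing a session is not the same as leaving the study, and referral is not withdrawal. This stands, and it is why the point is about what the session trigger permits. It also leaves two wordings that differ and no sentence that settles which was followed.

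Three stronger readings are tempting and are not supported.

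- *The change is overstated.* A reader might infer this as fact. Referral for danger signs does point that way, but SPs who stop because they feel better, or who improve after referral, would remove or reverse the bias. Their outcomes are not reported.
- *The trigger causes all the loss.* SPs who truly cannot be found would lack a score under a fixed-time visit too. The point applies to those who stopped or were referred but could still be surveyed.
- *The session schedule contradicts itself, and follow-up may be as short as two and a half months.* The 15 days is a minimum before the app unlocks the next session, and the same section says sessions coincide with scheduled monthly visits. The statements are compatible, and the 75-day floor is not a baseline-to-end-line interval. The Discussion reports flood disruption and delay, but not that delay differed between participants.

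It is also fair to say that methods for missing data are often left to a fuller plan, and that inflating the sample for attrition is ordinary practice. Neither is criticised here. The point rests on a trigger that the article does state.

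**Conclusion.** The concern holds in a limited form. The section that defines the end line ties it to the sixth session, with no time from enrolment. Taken literally and analysed with paired tests, that gives the change among people who completed six sequential sessions, at varying follow-up, under a label that covers all SPs. The result may overstate the change among all SPs.

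At the planned 10% attrition the possible overstatement is 0 to 0.30 PHQ-9 points against a planned change of 1.5. This assumes that completers improve by 1.5 and that those without an end line score lie between an equal improvement and a worsening of 1.5. The sign reverses if they improve more than completers, and the size doubles if 20% rather than 10% lack a score. If every enrolled SP was in fact surveyed, the selection problem disappears and only the timing remains to be clarified.

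**What to change.** Reconcile End Line Quantitative Assessment with the Study Procedure Outline. Define the outcome as PHQ-9 and GAD-7 sought from every enrolled SP at a set time from enrolment, whatever the number of sessions received or referral status.

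The data are already collected, so for the present analysis:

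- State whether end line was sought from all 98 SPs. Report how many have a score, by sessions completed and by referral status.
- Make the primary estimate cover all 98, using every available end line score and multiple imputation from baseline score, sessions completed and referral.
- Add scenarios in which missing end lines show no change and in which they show worsening. These matter most if few or no referred SPs have an end line score, because imputation for that group would then be extrapolation.
- Report the distribution of the baseline-to-end-line interval, since a set time can no longer be imposed.
- Label any result restricted to six-session completers as secondary.

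The cost is some additional analysis and reporting, plus the counts and dates needed from the study's own records. The main downside is that the estimate may be less favourable.

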**Methods:**

Project mPareshan is a single-arm, pre- and posttest implementation research trial in Badin District, Sindh, using mixed methods of data collection executed in 3 phases (preintervention, intervention, and postintervention). In the preintervention phase, formative qualitative assessments through focus group discussions and in-depth interviews assess the acceptability and appropriateness of intervention through perceptions of all concerned stakeholders using a specific interview guide. A REDCap (Research Electronic Data Capture)-based baseline survey using Patient Health Questionnaire-9 (PHQ-9) and Generalized Anxiety Disorder-7 Scale (GAD-7) determines the point prevalence of depression and anxiety among consenting men and women older than 18 years. Individuals with mild and moderate anxiety and depression are identified as screen positives (SPs) and are eligible for mPareshan app–based intervention. Mental health literacy of health workers is improved through customized training adapting the World Health Organization’s Mental Health Gap Action Programme guide 2.0. The intervention (mPareshan app) consists of tracking, counseling, and referral segments. The tracking segment facilitates participant consent and enrollment while the referral segment is used by LHWs to transfer severe cases to the next level of specialist care. Through the counseling segment, identified SPs are engaged during LHWs’ routine home visits in 6 face-to-face 20-minute counseling sessions over 6 months. Each session imparts psychoeducation through audiovisual aids, breathing exercises, and coping skills to reduce stress. Clinical and implementation outcomes include change in mean anxiety and depression scores and identification of facilitators and barriers in intervention uptake and rollout.

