	Qualitative data	Quantitative data		Intervention rollout^a^		Qualitative data		Quantitative data		
	FGDs^b^ and IDIs^c^	HH^d^ survey, PHQ-9^e^, and GAD-7^f^	mhGAP^g^-based training	Regular feedback received through mPareshan app		FGDs and IDIs		End line survey, PHQ-9, and GAD-7		
What is the point prevalence of anxiety and depression among a sample of rural households?		✓							Establishing prevalence of mild, moderate, and severe symptoms of anxiety and depression in Badin District.	
Is it feasible to implement an mHealth^h^-based mental health intervention through LHWs^i^ at community doorsteps?	✓					✓			Acceptability of LHW or LHS^j^ for using mPareshan app in managing anxiety and depression. Perceived barriers and facilitators in using the mPareshan app.	
Is there a change in CHW knowledge and skills in assessing, diagnosing, and managing anxiety and depression because of mPareshan mhGAP-based training?			✓						Capacity building of LHS and LHWs through mPareshan training.	
Is there any change in anxiety and depression scores of SPs^k^ because of mPareshan intervention?		✓						✓	Change in anxiety and depression scores of SPs. Operability, usefulness, and task-technology fitness of mPareshan app to the end users.	

^a^Intervention described in the last figure.

^b^FGD: focus group discussion.

^c^IDI: in-depth interview.

^d^HH: household.

^e^PHQ-9: Patient Health Questionnaire-9.

^f^GAD-7: Generalized Anxiety Disorder-7 Scale.

^g^mhGAP: Mental Health Gap Action Programme.

^h^mHealth: mobile health.

^i^LHW: lady health worker.

^j^LHS: lady health supervisor.

^k^SP: screen positive.

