#### Baseline Quantitative Assessments

##### HH Survey

A baseline survey was conducted in 5 Talukas of Badin District, Sindh to identify individuals having symptoms of anxiety and depression. Trained field staff visit HH for data collection. Data collectors are provided training on administering the GAD-7, PHQ-9, and entering data electronically using REDCap (Research Electronic Data Capture; Vanderbilt University) on a tablet. Data are also collected on basic sociodemographic variables.

The GAD-7 scale is used to screen symptoms of anxiety disorders. This scale has 7 items, and each item is rated on a sliding scale of 0-3 based on the frequency of occurrence of the symptoms. The maximum possible score is 21 and the minimum score is 0. Scores of 5, 10, and 15 are taken as the cutoff points for mild, moderate, and severe anxiety, respectively. GAD-7 has 89% sensitivity and 82% specificity for detecting generalized anxiety disorder at a cutoff score of 10 [35].

The PHQ-9 screens for symptoms of depression. There are 9 items rated on a scale of 0 to 3. The maximum possible score is 27 and the minimum score is 0. Scores 5, 10, 15, and 20 represent cutoff points for mild, moderate, moderately severe, and severe depression, respectively. PHQ-9 has 88% sensitivity and 88% specificity for detecting major depression at a cutoff score of 10 [36].

Participants with mild or moderate symptoms of anxiety and depression on the GAD-7 and PHQ-9 are identified as SPs and invited to take part in the mPareshan app–based counseling sessions.

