### Phase 2: Intervention Rollout

#### Eligibility Criteria for Participant Enrollment in Intervention

Residents who are 18 years of age and older, who are SP for “mild” or “moderate” symptoms of anxiety or depression as determined by the GAD-7 and PHQ-9, are recruited for the mPareshan intervention. Individuals receiving therapy or pharmacological treatment for mental health issues and exhibiting severe anxiety or depression with danger signs (self-harm, harm to others, and suicidal ideation) are not included in the study.

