## Discussion

Project mPareshan will assess the feasibility of using frontline workers in early home-based screening of anxiety and depression, providing app-based mental health counseling and prompt referrals. The community will ultimately benefit as the mental well-being of the population improves by a projected decrease in mean symptomatic scores of anxiety and depression. The contextually adapted mhGAP training for health workers will also lead to an improvement in their mental health literacy thus building the capacity of the primary health care workforce in mental health service delivery.

Previous studies using mHealth modalities have used cellular devices for the purpose of making referrals and record-keeping [26]. Despite the high reported suicide rate, there is a lack of awareness about mental health and the availability of specialized mental health services is suboptimal in Badin District. The novel approach being tested in this trial is expected to improve the mental health of rural populations where access to health care is limited and difficult. Results from this study will be important in initiating a policy dialogue for horizontal integration of basic mental health counseling initiatives in the current primary health system of low-resource settings.

Implementation challenges in this trial in the field included partial disruption and delay in intervention execution attributed to natural disasters, for example, floods in 2022. Furthermore, fluctuations in internet connectivity partially compromised the delivery of the app-based counseling sessions initially. The current substantial workload of LHWs makes it difficult to add mental health counseling as part of their routine package of service delivery. Moreover, considering the small sample size of participants enrolled for receiving the intervention, the generalizability of study findings may be an issue.

Based on the anticipated results of this pilot project, mental health can be introduced as part of the LHW curriculum and service delivery package. This will set the stage for integrating mental health into primary health care.

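### The screening score is also the 'pre' score, so the uncontrolled pre-post change cannot be read as effectiveness

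*Protocol article*

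**What the plan says.** The design has one group: "Project mPareshan is a single-arm, pre- and posttest implementation research trial in Badin District, Sindh". Under HH Survey, "Participants with mild or moderate symptoms of anxiety and depression on the GAD-7 and PHQ-9 are identified as SPs", and the bands are given there: "Scores 5, 10, 15, and 20 represent cutoff points for mild, moderate, moderately severe, and severe depression, respectively". The section on eligibility for the intervention words the rule differently, with 'or' in place of 'and': people with mild or moderate "symptoms of anxiety or depression as determined by the GAD-7 and PHQ-9, are recruited for the mPareshan intervention".

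Table 1 ticks that same household survey and the end line survey as the two data sources for the question whether scores change "because of mPareshan intervention". Data Analysis compares baseline with end line by a paired test and reports the mean difference with its 95% CI. End Line Quantitative Assessment then gives the interpretation: "This determines the change in mean symptomatic scores of anxiety and depression among intervention recipients (SPs), indicating intervention effectiveness (clinical outcome".

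The Study Procedure Outline places the survey before the training of health workers, and after the training says: "Next, the mPareshan app is developed based on stakeholder feedback acquired during the formative qualitative inquiry". Six monthly sessions follow, then the end line survey. No second symptom score before session 1 is described.

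**The concern.** One reading does two jobs: it admits people to the intervention because it is raised, and it is the value from which improvement is counted. A group chosen for raised scores is expected to score lower on retest, because part of each high reading is transient. The interval from survey to end line also covers training, app development and six months of sessions, so symptoms that remit on their own are counted as well. With no control group, neither can be separated from an effect of counselling.

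Zero change is therefore not what an ineffective intervention would be expected to produce. A significant paired test would not answer the causal question in Table 1 or support the effectiveness reading. This matters because that change is the article's stated clinical outcome, and the Discussion looks ahead to policy dialogue and to adding mental health to the health workers' curriculum and service package.

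**Working it through.** **1. The plan's own figure.** Sample Size Calculations gives a difference of 1.5 (11.61 - 10.1 = 1.51), SD 5.6, 5% significance and 80% power. The normal approximation is n = (5.6 x (1.960 + 0.842) / 1.5)^2 = 109.4, so 110. The exact two-sided paired t test needs 112 (power 80.2%), as stated. The arithmetic is sound. The issue is that the change is tested against zero.

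**2. Inputs for the no-effect drop.** From the article: mild or moderate PHQ-9 is 5 to 14, and 30% prevalence of symptoms is assumed. Not in the article, so assumed: the test-retest correlation r (0.6 to 0.9), the survey distribution (right-skewed, gamma shapes 0.7 to 1.5), and that the 30% means a score of 5 or more.

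**3. Selection on PHQ-9 alone.** Expected drop with no effect = (1 - r) x (SP mean - survey mean). Under these assumptions the survey mean is about 3.7 to 3.9 and the mean in the 5-14 window about 7.1 to 7.8. The gap is 7.1 - 3.7 = 3.4 to 7.8 - 3.9 = 3.9.

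| r | (1 - r) x 3.4 | (1 - r) x 3.9 |
|---|---|---|
| 0.9 | 0.34 | 0.39 |
| 0.8 | 0.68 | 0.78 |
| 0.7 | 1.02 | 1.17 |
| 0.6 | 1.36 | 1.56 |

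That is about 0.3 to 1.6 points. Simulating the window directly gives similar values.

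**4. Selection on anxiety or depression.** The formula in step 3 applies to selection on the outcome itself, so this rule has to be simulated. With both scores capped at 14 and an assumed correlation between the scales (0.6 in the check), the PHQ-9 drop is about 0.1 to 1.0. It is smaller because people admitted on GAD-7 alone need not have a raised PHQ-9. Under the 'and' rule it is larger than under 'or'.

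**5. If the 30% means scores of 10 or more.** The window then sits close to the survey mean. In one skewed example (survey SD 4, r = 0.8) the survey mean is 7.98. The SP mean is 8.33 on PHQ-9 alone and 7.62 under 'or', and the simulated drops are 0.01 and -0.08. Over all distributions tried, with r from 0.5 to 0.8, the range is about -0.5 to +1.0. The upper end needs a symmetric distribution and selection on PHQ-9 alone.

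**6. Consequence for the test.** Results reports 98 SPs recruited. With SD 5.6 the standard error is 5.6 / sqrt(98) = 0.566, and a drop of 1.985 x 0.566 = 1.12 is significant. From the noncentral t distribution:

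| Spurious drop | Noncentrality (drop / 0.566) | Significant improvement |
|---|---|---|
| 0.3 | 0.53 | about 8% |
| 1.0 | 1.77 | about 42% |
| 1.4 | 2.47 | about 69% |

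The nominal rate in the direction of benefit is 2.5%. These figures assume that all 98 have an end line score.

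**The case against.** The article is open about having one arm and calls itself a feasibility trial and a pilot, for which a single arm is acceptable. The abstract states the outcome neutrally, as change in mean scores. That stands, and the design need not change. It does not rescue the effectiveness and 'because of' wording, and the limitations in the Discussion (floods, connectivity, workload, small sample and generalizability) mention neither regression to the mean nor remission.

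A reader might infer that regression to the mean explains most or all of the planned 1.5 points. Putting the planning mean of 11.61 into the formula seems to show this: (1 - 0.8) x (11.61 - 4) = 1.52, or 1.32 with a survey mean of 5. The inputs do not fit together. If 30% score 5 or more, the 5-14 window gives an SP mean of about 7 to 8, not 11.61. Only r near 0.6 with selection on PHQ-9 alone approaches 1.5, and the eligibility section's 'or' rule does not reach it. The upper cut-off at 14 also offsets part of the regression, so even the direction is likely rather than certain.

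A reader might also infer that the floods distorted the baseline. The article reports "partial disruption and delay in intervention execution attributed to natural disasters, for example, floods in 2022" and says only that data were collected in 2022-2023. Without survey and session dates, no effect on the scores can be claimed, and splitting 98 people by flood timing would be imprecise and would not isolate a cause.

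**Conclusion.** The structural fault is in the article's own text: the survey scores that select SPs are also their 'pre' scores, no control group or second pre-treatment score is described, and the raw change is read as effectiveness. A paired test against zero cannot support that.

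The size is conditional. With 30% scoring 5 or more and r from 0.6 to 0.9, the spurious PHQ-9 drop is about 0.3 to 1.6 points for selection on PHQ-9 alone and about 0.1 to 1.0 under the 'or' rule, before any natural remission. With 30% scoring 10 or more it is near zero or reversed for skewed scores. The same reasoning applies to GAD-7, for which the article gives no planning values. The documents do not show that the whole planned effect is an artefact, nor that counselling has no effect.

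**What to change.** 1. In Table 1 and in End Line Quantitative Assessment, replace the causal wording with: *uncontrolled pre-post change; not attributable to the intervention alone*. Add regression to the mean and natural remission to the limitations in the Discussion.

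2. Reconcile 'and' under HH Survey with 'or' in the Study Procedure Outline and the eligibility section, and state the rule actually applied. Using that rule and the score distribution of the 366 people surveyed, report for each scale the drop expected with no effect at r = 0.6, 0.7, 0.8 and 0.9. Set it beside the observed change, and give the r at which the observed change would be fully explained. Label this a sensitivity analysis. Do not subtract it and present the remainder as an adjusted effect with a CI, because r is assumed and the interval would not carry that uncertainty.

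The cost is a few hours of analysis on data already held and a weaker effectiveness claim. The design and the data collection are unaffected.
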